#### Collaborative analysis

We will engage the CWG using Collaborative Yarning to seek guidance before finalisation of the items, particularly when interpreting MI results and determining whether any identified differences across sociodemographic groups represent meaningful variation or measurement concerns. At the end of Phase 4, we will have a final pictorially-supported well-being measure with culturally-responsive artwork developed through community co-design and feedback, which will be taken forward to Phase 5 for preference elicitation testing.

### Phase 5: Preference scoring system development

In Phase 5, guided by the CWG, we will use Best Worst Scaling (BWS) methods to develop a preference scoring system for the well-being measure, which will be a scoring option for the measure alongside total and factor summative scoring. We will use best practice methods^55^ and follow approaches taken in our existing project with youth^23^ and other studies with children.^27^,^29^ This approach will allow development of a scoring system for each item response level to estimate overall and dimension specific preference-based well-being scores on a 0–100 scale.

#### Knowledge holder recruitment

We will recruit in the order of 400 children via our partner organisations and through investigator and team networks. They will be invited to participate in this survey through email invitations to parents/carers and direct approaches through partner organisations. A broad range of children will be included (ensuring diversity in age, sex and remoteness) to enable us to examine any differences across sociodemographic and geographical groups. The BWS survey will take approximately 20 min to complete. Partner organisations include community-controlled health services, schools, and Aboriginal and Torres Strait Islander community organisations engaged through our existing networks. Survey items will be randomised in presentation order to minimise order effects.

#### Data collection

The BWS survey will be administered online, and children will enter a draw to win a prize. The survey will consist of around 10–12 questions which present two well-being item/response category statements, based on the final measure developed in Phase 4. Children will be asked to choose which statement they think is the ‘best’ in relation to how it would make them feel, that is, their well-being. We have successfully used this method previously with adults and youth; Ratcliffe *et al* have used this approach with slightly older children in CHU9D (Child Health Utility 9D) development.^27^,^29^

#### Sample size

The optimal sample size for a BWS survey is dependent on the final number of well-being items and response levels to be included in the descriptive system.^56^ Based on our previous measure development, we anticipate that there will be 16–18 items in the final measure. It is not feasible to present all combinations of well-being items to all children, therefore we will use a balanced incomplete block design.^57^ Given large sample properties can be achieved with around 50 respondents per block or version,^27 29 55 58^ a design with 8 blocks and around 50 respondents/block (n~400) will be robust enough to estimate main effects, first order interactions and examine differences between subgroups. This sample size is also consistent with previous successful applications of this method.^2729 58^,^61^

#### Statistical analysis

The relative importance of all items and response levels (referred to as statements) is given by the regression coefficients from a multinomial logit regression model. The absence or presence of a statement in a BWS task is coded as 0 or 1. For regression analysis the statement chosen as ‘best’ in each question will be coded as ‘1’ while the item chosen as the ‘worst’ is coded as ‘−1’. Since these values are on the same interval scale, a linear transformation can be applied to the dimension level values to ensure that the highest well-being state (ie, the sum of the best level of all dimensions) has a value of 100 and the lowest well-being state has a value of 0.

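### Phase 5 shows children two statements and asks only for the best, yet the analysis codes a chosen worst as −1; the task and the coding must be reconciled

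*Protocol article*

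**What the plan says.** Three parts of Phase 5 in the protocol article bear on this.

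- **Data collection.** The survey has "around 10–12 questions which present two well-being item/response category statements". On the response it says: "Children will be asked to choose which statement they think is the ‘best’ in relation to how it would make them feel". It describes no second question about the worse statement.
- **Statistical analysis.** Statement weights are the "regression coefficients from a multinomial logit regression model". On coding, "The absence or presence of a statement in a BWS task is coded as 0 or 1", and the "statement chosen as ‘best’ in each question will be coded as ‘1’ while the item chosen as the ‘worst’ is coded as ‘−1". The weights are then rescaled linearly so that the worst and best states score 0 and 100. The section does not say how many observations one question contributes, and it names no variance estimator.
- **Sample size.** The article says that "a design with 8 blocks and around 50 respondents/block (n~400) will be robust enough to estimate main effects, first order interactions" and comparisons between subgroups. It expects 16–18 items in the final measure and does not give the number of response levels.

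**The concern.** The data collection section describes a paired comparison: two statements, one answer. The analysis section describes best-worst data, in which a respondent makes two choices and each has its own code. Both are positive statements about the same survey, so this is not detail that a condensed article leaves to a fuller plan.

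The mismatch matters because best-worst data can be analysed by entering the best choice and the sign-reversed worst choice as two choice observations per question. With three or more statements the second choice carries new information. With two it repeats the first. An analyst following the coding paragraph literally could therefore duplicate every answer. Intervals on the weights, and the interaction and subgroup comparisons that the sample size section says about 400 children will support, would then look more precise than the data allow.

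**Working it through.** **The plan's own figure.** 8 blocks × 50 respondents = 400, which agrees with the stated n. No alpha, power or effect size is given for Phase 5, so there is no power calculation to reproduce.

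**Answers collected.** 400 children × 10 to 12 questions = 4,000 to 4,800 binary answers. Entering a best row and a worst row for each would give 8,000 to 9,600 rows from the same answers.

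**Likelihood for one pair.** Let c be the chosen statement, u the unchosen one, x their indicator vectors and β the statement weights.

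- Best row: P(c is best) = 1 / (1 + exp(−(x_c − x_u)β)).
- Worst row, sign reversed: P(u is worst) = 1 / (1 + exp(−((−x_u) − (−x_c))β)) = 1 / (1 + exp(−(x_c − x_u)β)).

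The two terms are identical. Stacking them doubles the log-likelihood, with these results:

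- The maximum, and so every coefficient, is unchanged.
- The information doubles, so the model-based standard error is multiplied by 1/√2 = 0.707, which is 29% too small.
- z statistics are multiplied by √2 = 1.414, which is 41% too large.
- A nominal two-sided 5% test rejects when |Z| > 1.96/√2 = 1.386, which has probability 0.166.

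**Simulation check.** 400 children, 8 blocks and 200 replicates, with connected sets of pairs drawn at random from different items. The response levels, the true coefficients and independence between a child's answers are assumptions, because the article gives none of them.

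| Items × levels, questions | SE, one row per pair | SE, stacked | SE, stacked and clustered by child |
|---|---|---|---|
| 17 × 1, 11 | 0.1294 | 0.0915 | 0.1291 |
| 16 × 3, 10 | 0.3415 | 0.2414 | 0.3412 |
| 18 × 3, 12 | 0.3376 | 0.2387 | 0.3371 |

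The ratio of stacked to single-row standard errors is 0.7071 in each case. The proportion of nominal 95% intervals missing the true value, in the same order of settings, was:

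- one row per pair: 3.9%, 4.3% and 5.8%;
- stacked: 14.3%, 15.2% and 18.1%;
- stacked with clustering by child: 4.1%, 4.4% and 6.0%.

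Stacking gave the same coefficients as one row per pair in every replicate.

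**The case against.** The strongest reply is that the article never says each question yields two observations. With two statements, coding 1 and −1 can be read as a single contrast: +1 for the picked statement, −1 for the other, 0 for those not shown. That is a correct paired-comparison analysis and has no shrinkage. This stands. The separate 0/1 coding of presence leans towards ±1 being a response code, but it does not settle the matter.

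Second, even stacked rows do harm only with unclustered model-based standard errors. The article names no variance estimator, and a condensed article may leave that to the analysis plan. This also stands, so the 29% and 16.6% figures need two unstated choices together.

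Third, the main product of Phase 5 is the set of weights rescaled to 0–100, and duplication does not move them. That is correct. The article also sets no alpha or formal test for Phase 5, so the exposure is limited to intervals, interactions and subgroup comparisons.

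A reader might go further and infer that the rule of about 50 respondents per block was taken from tasks showing more statements per question, so that 400 is too few here. The documents do not support this. The rule rests on cited sources that are not at hand, and the article does not say how many statements those studies showed. It describes the two-statement method as one the team has used before, with a sample size in line with earlier applications.

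None of these replies removes the mismatch: the analysis still refers to a choice that the survey, as described, does not ask for.

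**Conclusion.** The data collection and statistical analysis sections of Phase 5 contradict each other as written. The described task yields one best choice per pair, and the coded worst is only its complement.

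A reader might conclude that the plan double-counts answers and that its standard errors will be too small. That goes beyond the text. The effect (standard errors × 0.707, a 5% test at about 16.6%) follows only if best and worst are stacked as separate observations and the variances are model-based and unclustered. Otherwise duplication has no effect. In every case the coefficients and the 0–100 scores are the same.

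This should be corrected, but it is not a critical flaw. The contradiction is certain; its consequence for inference is conditional.

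**What to change.** Make the two sections describe the same task, in one of two ways.

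1. **If the two-statement task is intended:** call it a paired comparison. Fit a conditional (binary) logit with exactly one observation per question, with regressors +1 for the first statement shown, −1 for the second and 0 for those absent. The response is which statement was chosen, and standard errors are clustered by child. Delete the response coding of best as 1 and worst as −1.
2. **If a true best-worst task is intended:** amend the data collection section to show at least three statements per question and to ask for both the best and the worst.

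The first option costs a rewording of two paragraphs and a matching analysis script; intervals are wider only in comparison with an analysis that would have stacked the answers. The second also changes the survey and asks more of each child per question. The Methods section reports that Phase 2 data collection is under way, so either change can be made before Phase 5 begins.

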#### Collaborative analysis

At critical points during the statistical analysis process, the CWG will be convened to inform the iterative development of the final scoring.

## Ethics and dissemination

Ethics approvals have been obtained for this study from: the University of Queensland Human Research Ethics Committee (Ref: 2023/HE000607); Western Australian Aboriginal Health Ethics Committee (Ref: WAHREC1260); Far North Queensland Human Research Ethics Committee (Ref: 2023/QCH/99346); Aboriginal Health and Medical Research Council of New South Wales (Ref: 2140/23); Aboriginal Health Council of South Australia (Ref: 04–23-1063); Menzies School of Health Research and Northern Territory Department of Health Human Research Ethics Committee (Ref: HREC 2023–4608); and the Australian National University Human Research Ethics Committee (Ref: H/2024/0914). Approvals from the Departments of Education were obtained in each state and territory where school sites were engaged in the project. Each team member attending sites attained the relevant jurisdictions’ Working with Children Check. Results will be published in international peer-reviewed journals and presented at conferences, and summaries will be provided to the study partner organisations and other relevant organisations for broader dissemination. Children will receive study communications via their partner organisations in appropriate formats.

## Methodological limitations

Methodological limitations of this study include: the potential difficulty of recruiting sufficiently large and geographically diverse samples within proposed timelines, which will be managed through contingency recruitment plans and extended partner networks; the unproven feasibility of a 30-minute online survey for the youngest participants (aged 5–7 years), which will be addressed through piloting and adaptive design; and the challenge of applying Western psychometric validation frameworks within an Indigenist research design, which will be managed through CWG review of all interpretations to ensure community perspectives inform analytic decisions. The use of think-aloud yarns with Aboriginal and Torres Strait Islander children is novel and involves methodological adaptation, the outcomes of which will be documented and reported to support future replication.

